### 8.2 Statistical Analysis

Reduction in total cholesterol level at three months (from the baseline value) will be compared between the two groups – cinnamon vs placebo – using ANCOVA. Intention to treat analysis will be adhered to in analysing the outcome data. Data analysis will be done using version 4.0 of the R statistical software.

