| 
Statistical Methods and Data Analysis:
 
Reduction in LDL level at three months (from the baseline value) will be compared between the two groups – cinnamon vs placebo – using ANCOVA. Intention to treat analysis will be adhered to in analysing the outcome data. Data analysis will be done using version 4.0 of the R statistical software.
                                                                                                                                                                                                                                                                                                                                                                                                                                                                                                                                                |

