### Primary Objective

Primary objective of this study is

- To evaluate the effect of a standardized *C. zeylanicum* extract on LDL levels in individuals with average LDL level between 100-190 mg/dL ( $100 \text{ mg/dL} \leq \text{LDL} < 190 \text{ mg/dL}$ )

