### 4.2 Primary and secondary endpoints

#### **Primary endpoint**

The primary endpoint is:

- Reduction in LDL levels after three months of treatment.

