#### **Secondary endpoint**

- Reduction in total cholesterol and triglycerides and/or effect on HDL levels
- Effect on serum glucose level related parameters (FBS, HbA1c)
- Effect on anthropometric parameters (weight, WC, HC, mid arm circumference)
- Effect on systolic and diastolic blood pressure.
- Occurrence of adverse events due to regular administration of *C. zeylanicum* extracts on liver and kidney function and the occurrence of self-reported side effects in individuals under study.

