#### **Primary effectiveness measures**

- Change in LDL levels from baseline to final follow-up at three months post randomization.

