## 8. STATISTICAL CONSIDERATION

### 8.1 Sample size

The sample size was calculated assuming that the IMP would reduce total cholesterol by 10 mg/dL using below formula [31]. Assuming a standard deviation of 40 for total cholesterol and a correlation of 0.9 between the baseline and three months measurement a sample size of 64 per group would give 90% power at a significance level of 0.05. Expecting a 15% dropout rate the final sample size required will be 150 (75 per arm).

$$N \approx 4\sigma^2(1 - \rho^2)(z_{1-\frac{\alpha}{2}} + z_{1-\beta})^2/\Delta^2$$

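### Section 8.2 applies the ANCOVA to total cholesterol, although the primary objective, primary endpoint and synopsis analysis all name LDL

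*Protocol*

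**What the plan says.** Section 8.2 names one variable for the between-group ANCOVA: "Reduction in total cholesterol level at three months (from the baseline value) will be compared between the two groups". The synopsis, under Statistical Methods and Data Analysis, has the same sentence with the other variable: "Reduction in LDL level at three months (from the baseline value) will be compared between the two groups".

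The sections that define the primary question agree on LDL:

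- Section 2, primary objective: the effect of the "extract on LDL levels in individuals with average LDL level between 100-190 mg/dL".
- Section 4.2, primary endpoint: "Reduction in LDL levels after three months of treatment".
- Section 4.3, primary effectiveness measure: "Change in LDL levels from baseline to final follow-up at three months post randomization".
- Section 4.1 and the synopsis design paragraph also identify LDL as the primary outcome.

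Total cholesterol appears in section 4.2 among the secondary endpoints: "Reduction in total cholesterol and triglycerides and/or effect on HDL levels". Section 8.1 nevertheless sizes the trial on it, "assuming that the IMP would reduce total cholesterol by 10 mg/dL".

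**The concern.** The variable carried into the confirmatory test is the first thing an efficacy protocol has to fix, and here the body's analysis section fixes it differently from the endpoint sections. An analyst, or the author of a statistical analysis plan, who works from section 8 would compare total cholesterol and leave the LDL question unanswered. One who works from the synopsis would compare LDL and contradict section 8.2.

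Both routes can be defended from the text. If the choice is made once results are known, the 5% error rate no longer holds, and nobody could later show that the choice was independent of the data.

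This is not detail that a protocol may leave to a later plan. Section 8.2 is not silent; it states a variable, and that variable conflicts with the primary endpoint.

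**Working it through.** **1. The places side by side**

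| Place in the Protocol | Variable | Role |
|---|---|---|
| Synopsis, Objectives and Criteria for Evaluation | LDL | primary |
| Synopsis, Statistical Methods and Data Analysis | LDL | variable in the ANCOVA |
| Section 2, Primary Objective | LDL | primary |
| Section 4.1 | LDL | primary outcome |
| Section 4.2, Primary endpoint | LDL | primary |
| Section 4.3, Primary effectiveness measures | LDL | primary |
| Section 4.2, Secondary endpoint | total cholesterol | secondary |
| Section 4.3, Secondary effectiveness measures | total cholesterol | secondary |
| Section 8.1 | total cholesterol | basis of the sample size |
| Section 8.2 | total cholesterol | variable in the ANCOVA |

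Every statement of the primary question says LDL. Both parts of section 8 say total cholesterol. No part of section 8 specifies an analysis of LDL.

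**2. The sample size in section 8.1**

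This shows whether section 8.2 could be a single stray word. The inputs from section 8.1 are a difference Δ = 10 mg/dL, SD σ = 40, correlation ρ = 0.9, α = 0.05 (two-sided, from the formula's α/2 term) and power 90%.

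- N = 4σ²(1 − ρ²)(z₀.₉₇₅ + z₀.₉₀)²/Δ²
- N = 4 × 1600 × 0.19 × (1.960 + 1.282)²/100 = 4 × 1600 × 0.19 × 10.507/100 = 127.8
- Per group: 127.8/2 = 63.9, so 64, as stated.
- Allowance for 15% dropout: 128/0.85 = 150.6 in total, against the stated 150, which is close enough.

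The arithmetic is sound, but for total cholesterol. Section 8 is therefore consistent within itself around a variable that the rest of the protocol ranks as secondary, so section 8.2 cannot be dismissed as an isolated slip.

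**3. Error rate if either variable could be presented as the primary result**

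Take two test statistics Z₁ (LDL) and Z₂ (total cholesterol), bivariate normal with correlation r, under no effect on either. The chance of at least one false positive at two-sided 0.05 is

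1 − P(|Z₁| < 1.96 and |Z₂| < 1.96).

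| Assumed r | At least one rejection, either direction | At least one rejection in the direction of benefit |
|---|---|---|
| 0.9 | 7.0% | 3.5% |
| 0.8 | 7.8% | 3.9% |
| 0.7 | 8.3% | 4.2% |
| Single test | 5.0% | 2.5% |

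The protocol gives no correlation between the two lipids, so the r values are assumptions and the rows show a range.

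**4. What section 8.1 says about LDL**

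The protocol gives no LDL effect, SD or correlation, so power for LDL cannot be derived. Putting assumed LDL values into the same formula, with 64 completers per arm, shows how far the answer can move.

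| Assumed LDL effect, SD, ρ | Power at 64 per arm | Per arm for 90% |
|---|---|---|
| 10, 30, 0.9 | 99% | 36 |
| 10, 40, 0.9 | 90% | 64 |
| 10, 30, 0.7 | 75% | 97 |
| 7, 30, 0.8 | 59% | 139 |

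This is a related gap. It matters here because correcting section 8.2 alone would leave section 8.1 sized for a secondary endpoint.

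**The case against.** The best defence is that the synopsis belongs to the protocol and does specify an ANCOVA of LDL under intention to treat. On that reading an LDL test exists and the document contains a mismatch rather than an omission. Section 8.2 also never calls its comparison primary or confirmatory, and presenting total cholesterol as the primary result would contradict every endpoint statement. The inflated error rate then arises only if someone disregards the stated primary endpoint after seeing data. It also counts rejections in the harmful direction, and a false claim of benefit alone rises from 2.5% to between 3.5% and 4.2%.

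Much of this is fair on degree. The loss of any LDL test is conditional on following section 8.2 to the letter, and the error rates are conditional on a late choice and on assumed correlations. They should not carry the argument.

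It does not remove the defect. The synopsis and the body disagree on the variable in one and the same sentence, and section 8.1 sides with the wrong version. A reader should not have to weigh sections against each other to learn which variable is tested.

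**Conclusion.** The point holds and must be fixed. Section 8.2 names the wrong variable for the main analysis, judged by the protocol's own objective, endpoint and effectiveness measure and by the synopsis. This rests on the text alone and needs no assumption.

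If section 8.2 is followed literally, the primary endpoint receives no test. If the conflict is left open and settled after the data are seen, the two-sided error rate rises from 5% to roughly 7% to 8%, given correlations of 0.9 to 0.7 between the test statistics. Confidence in the contradiction is high. The percentages only illustrate its possible size.

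**What to change.** Amend section 8.2 before unblinding so that it matches the synopsis and section 4.2:

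- The main analysis is an ANCOVA of the change in LDL from baseline to Visit 5, cinnamon against placebo, with baseline LDL as covariate. The (1 − ρ²) term in section 8.1 already presupposes adjustment for the baseline value of the outcome analysed. Once that outcome is LDL, the covariate is baseline LDL.
- Total cholesterol is analysed in the same way, as a secondary endpoint only.

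In the same amendment, reconcile section 8.1 with the LDL endpoint. Give the LDL effect, SD and correlation, and state the power that 75 per arm provides for LDL after dropout.

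The correction to section 8.2 is one or two sentences and changes no visit, measurement or treatment. The cost is that of a routine amendment. Section 13 requires notification of protocol changes to the regulatory authorities and participants, with re-consent where required.

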## 9. INFORMED CONSENT

The participant must personally sign and date the latest approved version of the Informed Consent form before any trial specific procedures are performed.

Written and verbal versions of the Participant Information and Informed Consent will be presented to the participants detailing no less than: the exact nature of the trial; what it will involve for the participant; the implications and constraints of the protocol; the known side effects and any risks involved in taking part. It will be clearly stated that the participant is free to withdraw from the trial at any time for any reason without prejudice to future care, without affecting their legal rights and with no obligation to give the reason for withdrawal.

The participant will be allowed as much time as wished to consider the information, and the opportunity to question the Investigator. Written Informed Consent will then be obtained by means of participant dated signature and dated signature of the person who presented and obtained the Informed Consent. The person who obtained the consent must be suitably qualified and experienced and have been authorised to do so by an Investigator. A copy of the signed Informed Consent will be given to the participant. The original signed form will be retained at the trial site.

## 10. RESPONSIBILITIES

### ***Responsibilities of investigator/s***

The investigator will ensure that this study is conducted in accordance with the principles of the Declaration of Helsinki, International Council for Harmonisation (ICH) guidelines, or with the laws and regulations of the country in which the research is conducted, whichever affords the greater protection to the study subject.

The investigator will submit this protocol, ICF, and any accompanying material to be provided to the subject (such as advertisements, subject information sheets, or descriptions of the study used to obtain informed consent) to an ERC. The investigator will not begin any study subject activities until approval from the ERC has been documented and provided as a letter to the investigator.

The investigator is responsible for obtaining written informed consent from each individual participating in this study after adequate explanation of the aims, methods, objectives, and potential hazards of the study and before undertaking any study-related procedures.

The investigator must assure that subjects' anonymity will be strictly maintained and that their

identities are protected from unauthorized parties. Only subject initials, date of birth, another unique identifier (as allowed by local law) and an identification code will be recorded on any form or biological sample submitted to the Sponsor, ERC, or laboratory.

The investigator is responsible for ensuring the study is conducted in accordance with the procedures and evaluations described in this protocol.

## **11. DISSEMINATION OF RESULTS**

Primary and secondary outcomes of the study will be disseminated via research publications.

## **13. ETHICAL CONSIDERATION**

This research project will be conducted with full compliance of research ethics norms, the Declaration of Helsinki and the GCP guidelines. Ethical clearance will be obtained from an Ethics Review Committee affiliated to the Faculty of Medicine, University of Kelaniya, Sri Lanka. The trial will also be registered at the Sri Lanka Clinical Trials Registry.

Any change in trial protocol will be notified to the relevant regulatory authorities and trial participants, with re-consent being taken from participants, if required.

